### Recruitment and power

The study sample size will (4070 in each arm) provide adequate power to detect a difference-in-difference in hospital mortality between the pre-intervention period and the post-intervention period. This estimate is based upon the number of patients who receive care compliant with the respective bundles and associated hospital mortality. Analyzing ED patients included in the New York Sepsis Database, pre-intervention hospital mortality was 19.1% for those compliant with the 3-h bundle. Analyzing the data to create cohorts compliant with therapies at 1 h and at 3 h, the post-intervention hospital mortality of those receiving care compliant with the 1-h bundle was 16.2% and hospital mortality for those receiving care compliant with the 3-h bundle was 18.9% (preliminary data submitted to NHLBI R01 HL153268). This is based on the assumption that in the post-intervention period, the median time to antibiotics will be reduced by a quarter of an hour (25% reduction) in the 1-h arm. This quarter of an hour reduction in time to antibiotics translates to a 0.2% reduction in hospital mortality. Table 3 summarizes the assumptions used in the power calculation.

**Table 3 Tab3:** Assumptions for Donner and Klar’s cluster-randomized power calculation using a mixed model test for two proportions in a 2-level hierarchical design. An intraclass correlation coefficient of 0.025 is based on ED patients in the New York Sepsis Clinical Database

Compliant ED patients with the bundle	Pre-intervention mortality, %	Intervention period	Post-intervention mortality, %	Difference	Difference in difference
3-h arm	19.1		18.9	0.2%	2.7%
1-h arm	19.1		16.2	2.9%	

Using the power estimate methods of Donner and Klar, nine hospitals per arm with a minimum of 105 patients in each hospital will give 80% power to detect a 2.7% difference-in-difference in mortality, with *α* = 0.05, ICC = 0.025, and an equal number of hospitals per arm. To account for limitations in preliminary data, we increased the target number of patients by 50% to 158 patients. Since we expect bundle compliance in the 1-h arm to be 70%, 230 *total subjects* per hospital are needed. Table 4 shows the expected overall hospital mortality in the intent-to-treat analysis based on these assumptions. Multiple imputation will be used to handle missing data.

**Table 4 Tab4:** Estimated pre- and post-intervention overall mortality used in the intent-to-treat analysis

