### Anticipated findings and impact

We hypothesize that the 1-h bundle will be more effective than the 3-h bundle for reducing hospital mortality, respiratory failure, increasing ventilator-free days, and hospital (and ICU) length of stay. We additionally anticipate that use of the implementation strategy will improve compliance with both bundles. If these hypotheses are correct, improvement efforts should shift to adopt the 1-h bundle employing a rigorous implementation strategy. If there are no differences between the bundles, efforts should return to enhancing compliance with the 3-h bundle. A negative finding would be particularly important, since some hospitals are already focusing on the 1-h bundle in the ED. In addition, identification of sepsis phenotypes using routinely available clinical data may identify a specific groups of patients that benefit from an appropriately timed bundle.

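### The stated 80% power does not follow from the plan's own inputs, which give about 13% to 19%, and no valid reading of the sample size reaches 80%

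*Protocol article*

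**What the plan says.** In the Protocol article, Recruitment and power, the power statement reads "nine hospitals per arm with a minimum of 105 patients in each hospital will give 80% power to detect a 2.7% difference-in-difference in mortality". The inputs given for it are a significance level of 0.05, an ICC of 0.025 and equal allocation of hospitals. Whether the test is one- or two-sided is not stated. The Table 3 caption describes a "cluster-randomized power calculation using a mixed model test for two proportions in a 2-level hierarchical design" and adds: "An intraclass correlation coefficient of 0.025 is based on ED patients in the New York Sepsis Clinical Database". The mortality inputs are for bundle-compliant patients: "pre-intervention hospital mortality was 19.1% for those compliant with the 3-h bundle" (used for both arms), then 18.9% after the intervention in the 3-h arm and 16.2% in the 1-h arm.

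The 105 is raised by 50% to 158 and then, for 70% compliance, to 230 per hospital. The same section opens with "The study sample size will (4070 in each arm) provide adequate power".

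The Primary outcome analysis section makes the intention-to-treat difference-in-difference the primary analysis, using a logistic model with a random term for hospital. Anticipated findings and impact says that, if the bundles do not differ, effort should go back to 3-h bundle compliance. It adds: "A negative finding would be particularly important, since some hospitals are already focusing on the 1-h bundle in the ED".

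**The concern.** An ICC of 0.025 with only nine hospitals per arm sets a floor on the standard error that extra patients per hospital cannot lower in a post-period comparison. A 2.7-point difference in mortality of 16% to 19% is small against that floor. A difference-in-difference can remove stable hospital effects, but it adds the sampling error of two more groups. An 80% figure at 105 patients per hospital is therefore implausible on its face.

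The article also sets out what should follow from a null result. If true power is far below 80%, non-significance is expected even when the assumed benefit is fully real. Reading it as no difference between the bundles would then be unsupported.

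**Working it through.** **Inputs (Recruitment and power, Table 3).** 9 hospitals per arm; m = 105 per hospital (945 per arm); ICC 0.025; alpha 0.05, taken as two-sided with one-sided shown as well; mortality 19.1% before in both arms, 18.9% and 16.2% after; effect 0.027. Power is Φ(0.027/SE − 1.96). Adding the negligible opposite tail changes the results by less than half a point.

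**1. The stated figure by the named method (post-period, Donner and Klar).**
- Design effect = 1 + 104 × 0.025 = 3.6; effective n = 945/3.6 = 262.5 per arm.
- Variance sum = 0.189 × 0.811 + 0.162 × 0.838 = 0.2890.
- SE = √(0.2890/262.5) = 0.0332; 0.027/0.0332 = 0.81.
- Power = 13% two-sided, 20% one-sided. The stated 80% is not reproduced.
- Difference detectable with 80% power = 2.80 × 0.0332 = 9.3 points, holding the variance at the planned rates.

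**2. Can more patients or less clustering rescue it?**
- m = 230: design effect 6.725, SE 0.0306, power 14%.
- m unlimited: SE tends to √(0.2890 × 0.025/9) = 0.0283, power 16% (24% one-sided).
- ICC set to 0, m = 105: SE = √(0.2890/945) = 0.0175, power 34% (46% one-sided). Even without clustering, 346 per hospital would be needed.
- Keeping m = 105 and ICC 0.025, 80% power needs about 107 hospitals per arm.

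**3. The planned difference-in-difference, most favourable case.** Assume hospital effects are identical in both periods, so that they cancel. With n per arm per period, SE = √(0.975 × V/n), where V = 2 × 0.191 × 0.809 + 0.2890 = 0.5981 and 0.975 = 1 − ICC.

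| Patients per hospital per period | n per arm per period | SE | Two-sided | One-sided |
|---|---|---|---|---|
| 105 | 945 | 0.0248 | 19% | 29% |
| 158 | 1422 | 0.0203 | 27% | 38% |
| 230 | 2070 | 0.0168 | 36% | 49% |
| 452 (4070 read as per period) | 4070 | 0.0120 | 62% | 73% |

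Dropping the 0.975 lowers each figure by about one point or less. For 80% two-sided power, n = (2.80/0.027)² × 0.975 × 0.5981 ≈ 6,280 per arm per period, or about 700 per hospital per period.

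**4. Less than perfect stability (my assumption; the article gives no figure).** At 230 per hospital per period, a between-period hospital correlation of 0.9 gives 25% power and 0.8 gives 19%. The difference detectable with 80% power runs from 4.7 points (correlation 1.0) to 6.9 points (0.8).

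**5. The effect that the primary analysis targets.** Table 4 implies an intention-to-treat difference of 20.3 − 18.7 = 1.6 points after a common 23.2%. The best-case calculation in step 3 then gives about 14% power at 230 per hospital per period and 24% at 4070 per arm per period.

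**6. The sample size figures.** 158/0.70 = 225.7; 226 × 9 × 2 = 4068; 230 × 9 = 2070; 230 × 9 × 2 = 4140. The stated 4070 fits about 226 per hospital per period over both periods. It does not match the 230 given in the same section.

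**The case against.** **Some calculations do reach 80%.** Putting all 4070 per arm in the post period, with no clustering and no baseline contrast, gives 89%. Entering Table 3's within-arm changes, 0.2% and 2.9%, as if they were the two event rates gives SE = √((0.002 × 0.998 + 0.029 × 0.971) × 3.6/945) = 0.0107. That is 81% power one-sided and 71% two-sided at 105 per hospital. The second lands close to the stated figure and may be its source, but that is an inference. Neither is valid here. The first drops the plan's ICC and its primary contrast. The second uses the binomial variance of rates below 3% for an outcome at 16% to 19%.

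**Sidedness is not stated.** This stands, so both versions are shown. One-sided power is still 20% to 29% at 105 per hospital.

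**The model may be more efficient than a simple difference.** A baseline-adjusted comparison gives 21%, 39% and 63% at 105, 230 and 452 per hospital per period (74% one-sided at 452). Covariate adjustment may add precision, but the article gives no figure. At 105 per period it would have to cut the variance about seven-fold.

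**The post-period figures do not describe the primary test.** This is true. They show that the cited method does not give the cited result; the difference-in-difference figures describe the planned analysis. The correlations of 0.9 and 0.8 are sensitivity values only.

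**4070 is mostly rounding.** This largely stands. The gap from 4140 is 70 patients and hardly affects power. What needs clarifying is whether 230 is per period.

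**Conclusion.** The 80% claim is wrong on the plan's own inputs. Two-sided power for 2.7 points at 105 patients per hospital is 13% by the named method and 19% for the best-case difference-in-difference. At the enlarged size of 230 per hospital per period it is 36% at best. No reading that keeps the plan's mortality rates together with its ICC or its difference-in-difference reaches 80%. The most generous give 62% to 63% two-sided and 73% to 74% one-sided, and they need 4070 per arm in each period, which is an unlikely reading.

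The post-period result rests only on figures in the article plus the choice of sidedness. The difference-in-difference figures also assume perfectly stable hospital effects, which favours the plan. For the 1.6-point intention-to-treat effect, best-case power is about 14% at 230 per hospital per period.

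The planned reading of a null result is therefore not supported. At 230 per hospital per period the best-case 95% interval is about ±1.96 × 1.68 = ±3.3 points, so an estimate of zero would not exclude the 2.7-point benefit.

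**What to change.** 1. Replace the 80% statement with the power and detectable difference of the actual design: 18 hospitals, one figure for patients per hospital per period, ICC 0.025, stated sidedness, and a stated range for the between-period hospital correlation.
2. Give these for the intention-to-treat difference implied by Table 4 as well as for the 2.7 points in compliant patients, since the primary analysis is intention to treat.
3. State the sample size once and label it by period. If 230 per hospital per period is meant, that is 2070 per arm per period and 4140 per arm in total; reconcile 4070 with this.
4. Reword Anticipated findings and impact so that a non-significant result is read from the confidence interval for the mortality difference, and not as evidence that the bundles are equivalent.

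The cost is wording in the protocol and the SAP, and a much less favourable power statement. It needs no new patients and no change to the conduct of the trial.

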### Analysis plan

#### Aim 1: 1-h bundle will have significantly lower patient mortality and improve all secondary outcomes

##### Primary outcome analysis

An intention to treat analysis of patient mortality in each arm will be evaluated in 2 ways: (1) the difference, in primary outcomes (hospital mortality), between the two arms during the 6-month baseline assessment and the 6-month outcomes assessment, and (2) the comparison between the first two differences (i.e., difference-in-difference estimation). This difference-in-difference analysis will be the *primary analysis* to assess the *primary hypothesis* of Aim 1: the 1-h bundle will result in lower mortality than the 3-h bundle. Both absolute and risk-adjusted hospital mortality will be reported. Random-effects logistic regression will evaluate all the mortality differences. The random term will be the hospital. This model will contain three binary risk factors: (1) 1-h arm vs. 3-h arm, (2) 6-month baseline period prior to randomization vs. 6-month outcome assessment phase, and (3) the interaction of these two terms. The effect of the intervention and the effect of the two time periods will be quantified by odds ratios while the differences in hospital mortality will be quantified by model probabilities. Additionally, the model will be adjusted for hospital level 3-h bundle compliance prior to intervention along with patient and hospital characteristics.

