## Methods

### Study design

This study is a pragmatic, cluster-randomized trial of 18 hospitals (9 in each arm) comparing the 1- and 3-h bundles in patients presenting to emergency departments (ED) with sepsis. We will use a hybrid type 2 effectiveness-implementation design [46] to evaluate (1) effectiveness outcomes, including mortality and respiratory failure, and (2) implementation outcomes, including compliance (Fig. 1). The multi-faceted implementation strategy will apply to both trial arms. Application of the Pragmatic Explanatory Continuum Indicator Summary [47–50] (PRECIS) tool identifies this trial as pragmatic (vs. explanatory) [51]. A cluster-randomized trial is appropriate for analyzing the comparative effectiveness of the 1-h bundle versus the 3-h bundle because of the impossibility of randomizing patients to a particular approach and the importance of implementation of bundles at the hospital level. This protocol adheres to the Standard Protocol Items: Recommendations for Interventional Trials (SPIRIT) guidelines [52]. Figure 2 provides a summary of the enrollment schedule, interventions, and assessments using the SPIRIT flow diagram.

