### Randomization

Hospitals will be randomized to one of two arms (1- or 3-h bundle) in a 1:1 ratio. Randomization will be accomplished using randomly permuted blocks of variable size and controlling for academic or community status. Hospital physician and nurse dyads will be told which condition they were randomized to during in-person meetings at SCCM immediately prior to the Implementation Phase; separate meetings will take place for each study arm. Each arm will undergo a 30-month structured, collaborative implementation approach to operationalize compliance with their bundle assignment. The elements of both bundles are identical—only the timing is different (see Table 1). In this cluster-randomized clinical trial, the hospital is the unit of randomization. Hospitals will be informed as to their randomized arm after the baseline collection period. The randomization will be done by the study statistician and held only in the statistician’s computer until the reveal meeting at the end of the baseline period. Due to the pragmatic, open-label design of this trial and its objective measurement of study outcomes, the study staff, investigators, sites, and biostatisticians will not be masked to treatment condition once randomization occurs. Patients will receive standard of care for sepsis and their data will be collected retrospectively by the hospital each month.

**Table 1 Tab1:** 1- and 3-h bundle elements: quality and outcome indicator definitions and specifications

	**Definition of bundle element (quality indicator) or outcome measure obtained from the EHR by site staff**	**Both study arms**

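### The primary difference-in-difference model makes no allowance for hospital-specific change between periods, so its test is anticonservative unless all hospitals in an arm would change alike

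*Protocol article*

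**What the plan says.** Protocol article, Analysis plan, Aim 1, Primary outcome analysis:

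- The model: "Random-effects logistic regression will evaluate all the mortality differences".
- The period factor: "6-month baseline period prior to randomization vs. 6-month outcome assessment phase". It enters alongside arm and the arm-by-period product.
- The test that decides the trial: "This difference-in-difference analysis will be the *primary analysis* to assess the *primary hypothesis* of Aim 1".
- The random part: "The random term will be the hospital".
- Covariates: "the model will be adjusted for hospital level 3-h bundle compliance prior to intervention along with patient and hospital characteristics".

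The randomised unit is the hospital, nine per arm, allocated "controlling for academic or community status" (Randomization). Table 3 describes the power model as having two levels and gives one ICC, 0.025; there is no period level. The two 6-month windows lie either side of a 30-month implementation phase (Adoption-preparation phase; Implementation phase; Sustainment phase). No section names a hospital-by-period effect or a random period slope.

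**The concern.** The treatment effect is a difference between arms in within-hospital change. A random intercept describes how hospitals differ in level, and level drops out of a change. What remains in the model's standard error is binomial sampling of patients. Real differences between hospitals in how far their mortality moves are set to zero.

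The design gives reasons to expect such differences. Each site forms its own change team, develops its own automated sepsis alerts and reviews its own order sets. Sites vary in size and teaching status, and reported SEP-1 compliance at entry could lie anywhere from 30% to 70%. Alerts built at each site can also alter which patients are identified.

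At stake is the error rate of the single primary test. Under Anticipated findings and impact, a positive result is meant to move improvement efforts to the 1-h bundle. An anticonservative test could credit that bundle with ordinary hospital drift. The Secondary outcomes and bundle compliance sections refer back to the same approach.

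**Working it through.** **Inputs.** 18 hospitals, 9 per arm (Study design). ICC 0.025 and alpha 0.05, taken as two-sided because sidedness is not stated (Recruitment and power). The windows are 6 months each with 30 months between, so midpoints are 3 + 30 + 3 = 36 months apart. The correlation of a hospital's effect between the two periods (the cluster autocorrelation, CAC) is not in the document; it is assumed and shown as a range.

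**Patients per hospital-period (m).** 158/0.70 = 225.7, and 225.7 × 9 hospitals × 2 periods = 4063, close to the stated 4070 per arm. In reverse, 4070/(9 × 2) = 226. The rounded figure in the text is 230. So m is 226 to 230.

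**The plan's power figure.** The stated 80% for a 2.7-point effect with 105 patients per hospital does not reproduce. Using 19.1% pre-intervention mortality in both arms and 18.9% and 16.2% afterwards, the p(1−p) terms sum to 0.598. The random-intercept SE of the difference-in-difference is √(0.598 × 0.975/(9 × 105)) = 0.0248, which gives 19.1% power. This is a separate problem, and nothing below depends on it.

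**Variance of the interaction.** Let σ² be the total variance.

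- Stated model, per hospital change: 2(1−ICC)σ²/m.
- With hospital-specific change: 2[(1−ICC)σ²/m + ICC(1−CAC)σ²].
- Ratio: 1 + m·ICC·(1−CAC)/(1−ICC).
- Type I error: 2[1 − Φ(1.96/√ratio)].

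For m = 226, m·ICC/(1−ICC) = 5.65/0.975 = 5.79. At CAC 0.9 the ratio is 1 + 0.579 = 1.58.

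The formula was checked by simulating the stated logistic model under no effect (about 22% mortality, m = 226, 1,500 trials per setting). The last column is a t-test with 16 df on the 18 hospital-level log-odds changes.

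| CAC | Variance ratio | True SE / model SE | Type I, formula | Coverage of 95% interval | Type I, simulated | Hospital-change t-test |
|---|---|---|---|---|---|---|
| 1.0 | 1.00 | 1.00 | 5.0% | 95% | 5.2% | 4.9% |
| 0.95 | 1.29 | 1.14 | 8.4% | 92% | 7.9% | 5.7% |
| 0.9 | 1.58 | 1.26 | 11.9% | 88% | 11.3% | 5.6% |
| 0.8 | 2.16 | 1.47 | 18.2% | 82% | 17.3% | 4.9% |

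With m = 230 the formula gives 8.5%, 12.0% and 18.4% at CAC 0.95, 0.9 and 0.8. A separate simulation at m = 230 and 20% mortality (600 trials per setting) gives 5.0%, 10.5% and 18.8% at CAC 1.0, 0.9 and 0.8.

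**Where the error arises.** In the 1,500-trial runs the model's mean SE for the interaction stayed at 0.110 at every CAC. The actual standard deviation of the estimate rose from 0.111 to 0.126, 0.137 and 0.162. Referring the stated model to t with 16 df still gave 6.1%, 9.0% and 14.9% at CAC 0.95, 0.9 and 0.8.

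**Sensitivity.** With m = 105 the simulated error is 7.1%, 9.5% and 10.5% at CAC 0.95, 0.9 and 0.8. If adjustment reduced the ICC to 0.01 (an illustrative value) with m = 226, the formula gives 6.3%, 7.7% and 10.4%.

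**Power with the change variance included.** At m = 226 the random-intercept SE is √(0.598 × 0.975/(9 × 226)) = 0.0169. Multiplying by the SE ratios gives 0.0192, 0.0213 and 0.0249. Power for 2.7 points, on a normal reference, is 35.7%, 28.9%, 24.5% and 19.1% at CAC 1.0, 0.95, 0.9 and 0.8.

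**The case against.** **The article is condensed and the SAP is not shown.** This stands for degrees of freedom, small-sample correction and permutation inference; their absence is no finding. It does not cover the random structure, which the article states outright and in the singular. The sentence could be read as naming only the grouping unit, leaving room for a random period slope, but that is not its plain meaning.

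**The size rests on an unknown correlation.** This stands. A reader might infer that the 5% test is bound to fail, or take error rates near 30% from a CAC of 0.6. The document supports neither: at CAC 1.0 there is no inflation, and nothing in the text fixes a value below that. Only the direction is certain once CAC is below 1.

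**Covariates and site selection limit drift.** This stands in part. Patient characteristics can absorb measured case-mix change, and a single EHR vendor with CMS time-zero criteria narrows differences in measurement. Pre-intervention compliance and fixed hospital characteristics do not vary over time, so as main effects they cannot absorb hospital-specific change.

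**Eighteen hospitals are simply few.** A reader might blame the number of hospitals. The t(16) results show otherwise: the missing term is the cause. The number of hospitals matters for the reference distribution once the term is present.

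**Subtracting the baseline and the stratification factor.** A reader might also fault the difference-in-difference itself, or the lack of a named stratum term. Subtracting the baseline is a legitimate choice, and academic or community status may already be among the hospital characteristics.

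**Conclusion.** The point holds, conditionally. As stated, the primary model gives valid inference only if all hospitals in an arm would change identically over about 36 months. For any CAC below 1 its intervals are too narrow and its test anticonservative. At the planned size and ICC 0.025, type I error is about 8% at CAC 0.95, 11-12% at 0.9 and 17-19% at 0.8, against 5% at CAC 1.0. These figures assume a two-sided test, equal hospital sizes and no reduction from case-mix adjustment.

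The percentages apply to mortality and should not be transferred to the other outcomes. Ventilator-free days and length of stay use different regression families, and the compliance section says only that its analysis is similar. The structural gap carries over wherever the hospital-only random term does. Because it concerns the one confirmatory test, it should be settled before outcome data are analysed.

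**What to change.** Add a hospital-by-period random effect to the primary model, beside the hospital intercept. Refer the interaction to about 16 degrees of freedom (18 hospitals less 2 arms), or use a permutation test that reassigns arms within the academic/community control used at randomisation. Comparing hospital-level changes between arms on 16 df is a simple equivalent, and it held 4.9% to 5.7% in the check above. Use the same structure for the secondary and compliance analyses that follow the primary approach.

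Possible wording: *The model will include random effects for hospital and for hospital-by-period; the arm-by-period interaction will be tested with a small-sample correction based on the number of hospitals.*

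This costs a short change of text and code and needs no new data. The statistical cost is wider intervals: by factors of about 1.14, 1.26 and 1.47 at CAC 0.95, 0.9 and 0.8, before the small-sample reference. Honest power is lower than the stated model suggests, so the power statement should be redone over a stated range of CAC.

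Constraining the arms to a common baseline, or adjusting for hospital baseline mortality instead of subtracting it, is an optional efficiency gain (about 7% to 24% of variance across CAC 1.0 to 0.6). It is not part of the correction.

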## Trial status

Baseline data collection for the trial began December 1, 2022. Sites will be randomized to the 1- or 3-h bundle at the end of June 2023. The trial is funded through June 2027.

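### The primary difference-in-difference subtracts in full a baseline arm difference that is zero in expectation; it is valid but less efficient than baseline adjustment, by a modest amount

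*Protocol article*

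**What the plan says.** The Primary outcome analysis section defines the estimate as "the comparison between the first two differences (i.e., difference-in-difference estimation") and states: "This difference-in-difference analysis will be the *primary analysis* to assess the *primary hypothesis* of Aim 1". The random-effects logistic model is set out as follows: "This model will contain three binary risk factors: (1) 1-h arm vs. 3-h arm, (2) 6-month baseline period prior to randomization" against the outcome assessment phase, and "3) the interaction of these two terms". On clustering it says only: "The random term will be the hospital". It adds that "the model will be adjusted for hospital level 3-h bundle compliance prior to intervention along with patient and hospital characteristics". Baseline hospital mortality is not named as a covariate.

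On timing, the same section describes the baseline as preceding randomisation. The Randomization section says: "Hospitals will be informed as to their randomized arm after the baseline collection period". Trial status says: "Sites will be randomized to the 1- or 3-h bundle at the end of June 2023", with baseline collection having begun on 1 December 2022. Tables 3 and 4 assume the same pre-intervention mortality in both arms (19.1% and 23.2%).

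**The concern.** An assignment made after the baseline cannot affect baseline mortality, so the baseline arm difference has expectation zero. The planned model still estimates it freely and subtracts 100% of it. The minimum-variance weight is r, the correlation between a hospital's baseline and outcome-period mortality proportions. Sampling noise alone puts r below 1. Any drift in hospital effects lowers it further, and the two six-month windows are separated by a 30-month implementation phase.

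Precision is at stake, and so is how the result reads when the baseline happens to be uneven. With nine hospitals per arm, a chance imbalance of several percentage points in baseline mortality is ordinary. The listed covariates may explain part of it, but they leave the free arm term in the model and do not replace baseline mortality.

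**Working it through.** **Plan's own figures.** Table 4 reproduces: 0.80 × 18.9 + 0.20 × 26.1 = 20.3% and 0.70 × 16.2 + 0.30 × 24.4 = 18.7%, an intention-to-treat difference of 1.6 to 1.7 points. The stated 80% power (9 hospitals per arm, 105 patients each, 2.7 points) does not reproduce. The design effect is 1 + 104 × 0.025 = 3.6, so effective n is 945/3.6 = 262.5 per arm. The SE for 18.9% vs 16.2% is then 3.32 points, and two-sided power is 12.6% for a post-period comparison. It is 19.3% for difference-in-difference with a stable hospital intercept. That is a separate problem; here it only sets the scale.

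**Inputs.**
- From the article: k = 9 hospitals per arm, ICC 0.025, mortality p = 23.2%.
- Inferred: m ≈ 230 patients per hospital per period. The article gives 230 in total per hospital without saying per period, but 4070/9 = 452 per hospital, or 226 in each of two periods.
- Assumed: CAC, the between-period correlation of the hospital effect, from 0.5 to 1.0. A single hospital intercept implies 1.0.

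**Formulas.** Let V be the variance of a one-period arm difference.
- V = (2/9) × 0.232 × 0.768 × (1 + 229 × 0.025)/230, so √V = 3.40 points. This is the SD of the chance baseline difference.
- r = m × ICC × CAC / (1 + (m − 1) × ICC) = 5.75 × CAC / 6.725.
- Var(difference-in-difference) = 2(1 − r)V; Var(baseline-adjusted) = (1 − r²)V; the ratio is 2/(1 + r).
- Estimating the slope from 18 hospitals inflates the adjusted variance by about 1 + 1/14, so the ratio is divided by 1.071.
- Over-correction for a 1-SD baseline imbalance: (1 − r) × 3.40 points.

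| CAC | r | Ratio, known weight | Ratio, slope estimated | Shift at 1-SD imbalance (points) |
|---|---|---|---|---|
| 1.0 | 0.855 | 1.08 | 1.01 | 0.5 |
| 0.8 | 0.684 | 1.19 | 1.11 | 1.1 |
| 0.5 | 0.428 | 1.40 | 1.31 | 1.9 |

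**Simulation** (20,000 trials, binomial counts, hospital-level t tests). The SD of the estimate is 2.68 (difference-in-difference) vs 2.54 (ANCOVA) points at CAC 0.8, and 3.62 vs 3.15 at CAC 0.5. At CAC 1.0 it is 1.78 for both. The slope of the estimate on the baseline imbalance is −0.32 and −0.58 for difference-in-difference at CAC 0.8 and 0.5, and about zero for ANCOVA. Both tests reject about 5% under the null. If 230 covered both periods (115 each), the variance ratios would be about 1.18 and 1.36 at CAC 0.8 and 0.5.

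**Power, difference-in-difference vs ANCOVA** (simulated with a normal approximation):

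| CAC | 2.7 points | 1.68 points (Table 4) |
|---|---|---|
| 1.0 | 28.6% vs 28.6% | 13.9% vs 14.1% |
| 0.8 | 15.3% vs 16.8% | 9.0% vs 9.4% |
| 0.5 | 10.7% vs 12.4% | 7.1% vs 7.7% |

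With a known weight and a normal reference the gain for 2.7 points would be 2.4 to 3.3 points (36.1% to 38.5% at CAC 1.0, 12.6% to 15.9% at CAC 0.5, m = 226). Estimating the slope and using t brings it below 2.

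**The plan's own random structure.** With one hospital intercept the model treats the hospital part of the change as zero. On a linear approximation, its SE is too small by the factor √[(0.975/230) / (0.975/230 + (1 − CAC) × 0.025)]. This is 0.79, 0.68 and 0.50 at CAC 0.9, 0.8 and 0.5. The corresponding null rejection rates are about 12%, 18% and 32%; simulation gave 12%, 18 to 19% and 33%.

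**Dropping only the arm term.** In a logistic simulation that kept the single intercept, the variance ratios were 1.04, 1.10 and 1.16 at CAC 1.0, 0.8 and 0.5. The slope on the baseline imbalance was still −0.13 at CAC 0.8 and −0.33 at CAC 0.5. Only part of the gain is recovered.

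**The case against.** The strongest reply is that nothing here is an error. Difference-in-difference in a randomised trial is a valid, pre-specified estimator, and the sample size is framed around it. Under the stability that a single hospital intercept implies, it loses essentially nothing at 230 per period. All of the larger losses rest on a CAC that the article does not supply. This stands, and it limits the point to efficiency.

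Four stronger readings are tempting and not supported:
- **That the primary estimate is biased.** Randomisation makes the baseline difference zero in expectation, not in the sample, and difference-in-difference is unbiased over randomisations.
- **That the conditional shift is harm on top of the standard error.** It is part of the reason the SD is 2.68 rather than 2.54 at CAC 0.8. It approaches or exceeds the intention-to-treat effect only towards CAC 0.5; at CAC 1.0 it is 0.5 points.
- **That substantial power is being discarded.** The gain is at most about 2 points.
- **That type I error is safe at 5%.** This holds for hospital-level t tests. The planned single-intercept model would be anti-conservative if CAC is below 1.

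The reply does not show any advantage for full subtraction. Across the range examined, ANCOVA with an estimated slope was never materially worse. Nor is the baseline worthless: difference-in-difference beats ignoring it whenever r exceeds 0.5. It falls behind at CAC 0.5 (theoretical SE, for 18.9% vs 16.2% and m = 226, 3.32 vs 3.10 points).

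**Conclusion.** The point holds as one of efficiency and conditional over-correction. The article fixes a free arm effect at a pre-randomisation baseline and so subtracts all of a difference whose expectation is zero. Relative to hospital-level ANCOVA the variance is about 1.0, 1.1 and 1.3 times as large at CAC 1.0, 0.8 and 0.5. This rests on ICC 0.025, 9 hospitals per arm, an inferred 230 or so patients per hospital per period, and CAC as an assumption. The improvement is cheap and modest, and power stays far below 80% with either analysis. The mechanism is certain; the size is not, because CAC is unknown. Wherever CAC is low enough for the efficiency loss to matter, the single hospital random term also understates the standard error, so the two should be changed together.

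**What to change.** In the Primary outcome analysis section, make the primary estimate baseline-adjusted:

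1. Preferred: analyse outcome-period mortality with each hospital's baseline-period mortality (for example its log-odds) as a covariate, plus the academic/community stratum used in randomisation.
2. Alternative: a constrained-baseline model on both periods. Drop the arm main effect and keep period, plus a treatment indicator equal to 1 only for 1-h hospitals in the outcome period. Include both hospital and hospital-by-period random terms.

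In either case specify a small-sample t reference with hospital-level degrees of freedom. With 18 hospitals, a constrained-baseline model tested with an ordinary Wald z rejected about 7% under the null in a linear approximation. Keep the difference-in-difference as a sensitivity analysis.

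The cost is wording, with no new data, and about one hospital-level degree of freedom for the baseline slope (16 to 15), already counted in the simulated results. The change should be made before outcome data are analysed.
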